### Randomization and data collection

Confirmed, eligible, and consented participants were randomly assigned to one of the two study groups (control or intervention) in a 1:1 allocation ratio. These participants were randomized using sex stratification (40% males and 60% females) and permuted blocks with random block sizes. For this randomization scheme, a sequence of block sizes was randomly generated in which allowable blocks were a random mix of sizes 2 or 4 participants. Thus, half of the participants within each block were randomly assigned to the control group and the other half to the intervention group.

Trained research assistants conducted all visits in a single private room at FDI. Research assistants were bilingual (English and Spanish) and trained in culturally sensitive interviewing, clinical protocols, data collection, data entry, confidentiality, and safety measures. Each clinical visit lasted ∼2 h. The counseling session lasted 1 h. Participants were compensated for their time up to $150, such that they received $50 at each of the three examination visits, with no monetary incentive at the counseling session. At the counseling session, participants received a bag with food (intervention group) or cooking utensils (control group). A light, healthy snack, and water were provided after each visit.

Participants were allowed to pause or terminate the interviews at any time. In such case, the participant was contacted up to five times within the subsequent 14 d to complete the pending questionnaires or measurements. Participants remained enrolled in the study for its duration (4 mo) unless they actively left the study, had a new ineligibility factor, or lost contact. All interview questions and outcome measures at 2  and 4 mo were assessed using the same protocols at baseline.

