### Statistical Analysis

Table 4 shows the minimum detectable effect sizes estimated for primary and secondary outcomes for the original sample size (n = 100) and adjusted sample size after COVID-19 protocols (n = 50), accounting for 10% loss-to-follow-up, using ANCOVA test [101] with 0.05 Type I error and 80% power.

**TABLE 4 tbl4:** Minimum detectable effect sizes (4 mo means adjusted for baseline) for primary and secondary outcomes for PROMED, using ANCOVA test for 80% power and 5% Type I error rate

	Mean (SD) at baseline	Empirical Corr. b∖w baseline and 4 mo values	MDE for n = 90 (45 per arm)	MDE for n = 44 (22 per arm)
10-item cardiometabolic improvement score	5.4 ± 1.4	0.94	0.28	0.40
Weight (lbs.)	201.2 ± 42.3	0.97	6.07	8.68
Waist circumference (cm)	42.9 ± 4.9	0.92	1.13	1.62
BMI (kg/m^2^)	34.2 ± 6.6	0.86	1.99	2.84
Systolic BP (mmHg)	123.4 ± 17.1	0.80	6.06	8.66
Diastolic BP (mmHg)	80.4 ± 9.3	0.49	4.79	6.85
Total cholesterol (mg/dL)	196 ± 46.5	0.59	22.17	31.71
LDL-C (mg/dL)	123.4 ± 37.4	0.83	12.32	17.62
HDL-C (mg/dL)	48.9 ± 12.4	0.83	4.08	5.84
Triglycerides (mg/dL)	118.2 ± 73.0	0.74	28.99	41.47
Glucose (mg/dL)	101.6 ± 29.4	0.80	10.42	14.90
Hemoglobin A1c (%)	6.0 ± 1.3	0.77	0.49	0.70
Diet quality (score)	35.2 ± 3.7	0.85	1.15	1.65
Diet satisfaction (score)	94.9 ± 18.9	0.85	5.88	8.41

BP, blood pressure; PROMED, Puerto Rican Optimized Mediterranean-like Diet. ∗The results account for 10% loss-to-follow-up for original sample sizes of n = 100 and n = 50. ∗∗The minimum detectable effect sizes (MDE) by the ANCOVA approach is calculated based on $MDE=\frac{4{\left(Z_{1-\frac{\alpha }{2}}+Z_{\beta }\right)}^{2}\left(1-Corr^{2}\right)SD^{2}}{n}$, where n is the sample size (active arm + control arm) after accounting for loss-to-follow-up, Corr is the correlation coefficient between the baseline and 4 mo values, SD is the standard derivation for the baseline value, $Z_{\tau }$ is the $\tau^{th}$ lower-quantile of the standard normal distribution, α=0.05 is the type I error rate, and β=0.8 is the power.

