The primary analysis is intention-to-treat. Data analysis will follow the Consolidated Standards of Reporting Trials (CONSORT) guidelines [102]. Flowcharts will include the number of participants at each stage, including screened, eligible, randomized, and followed-up. At the 4-mo follow-up, the mean cardiometabolic improvement score for participants in the intervention arm versus the control arm will be compared using a two-sample *t*-test. If randomization does not control for differences between the treatment and control groups on baseline characteristics, those differences will be statistically controlled for using multivariable regression modeling. Secondary analysis will compare the change in individual cardiometabolic risk factors and dietary and psychosocial factors between intervention and control groups using an ANCOVA test. Repeated measures analysis will test differences in 2- and 4-mo outcomes. Prespecified subgroup analyses will be conducted by sex-at-birth, BMI status, pre-existing cardiometabolic profile, COVID-19 period (pre- vs. at-pandemic), and adherence status. Missing data and loss to follow-up will be corrected. Two-sided 0.05 type I error threshold for statistical significance will be used.

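### The primary t-test leaves out the sex strata and adds covariates only where baseline imbalance is seen; one fixed, prespecified model would be modestly better and nearly free

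*Protocol article*

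**What the plan says.** All of this is in the protocol article.

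- **Randomisation and data collection:** participants were "randomized using sex stratification (40% males and 60% females) and permuted blocks with random block sizes", "in a 1:1 allocation ratio". Block sizes are 2 or 4.
- **Statistical Analysis, primary test:** at 4 months "the mean cardiometabolic improvement score for participants in the intervention arm versus the control arm will be compared using a two-sample" t-test. Sex is not in this comparison; it appears later as a subgroup factor.
- **Statistical Analysis, adjustment:** the next sentence reads "If randomization does not control for differences between the treatment and control groups on baseline characteristics, those differences will be statistically controlled for", and names multivariable regression as the means. It gives no criterion for a difference and no covariate list. It does not say whether the regression replaces the t-test as the primary result.
- **Statistical Analysis, error rate:** "Two-sided 0.05 type I error threshold for statistical significance will be used".
- **Table 4:** the planning figures use ANCOVA "with 0.05 Type I error and 80% power", with 22 per arm analysed after the target was cut from 100 to 50.

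**The concern.** Under sound randomisation, any baseline difference between arms is due to chance. A covariate earns its place in the model by predicting the outcome, and the size of the observed imbalance says little about that. The stated rule selects on the wrong property and lets the observed data decide the form of the analysis.

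Two prognostic candidates are already in hand. Sex was thought important enough to stratify on; omitting it leaves any between-sex variance in the standard error, so the t-test becomes slightly conservative wherever sex matters. Baseline risk is the other. The score counts changes past fixed thresholds on ten factors, and someone who starts high has more regression to the mean working in their favour.

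At stake are some precision in a trial whose sample was halved, and the certainty that there is only one primary p-value.

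**Working it through.** **1. The plan's own figure.** For the primary score Table 4 gives SD 1.4, correlation 0.94 and a minimum detectable effect of 0.40 at n = 44. The square root of the printed expression gives 2 × (1.960 + 0.842) × 1.4 × √(1 − 0.94²) / √44 = 0.403, so the figure is reproduced. Without the correlation term, as fits an unadjusted comparison, the result is 2 × 2.802 × 1.4 / √44 = 1.18. A true difference of 1.2 is therefore the natural place to compare models.

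**2. Power of the t-test.** With 22 per arm, the noncentrality is 1.2 / (1.4 × √(2/22)) = 2.843. On 42 degrees of freedom, two-sided 0.05, power is 79.3%.

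**3. Adding sex.** The documents give no sex effect, so 0.3 SD is assumed. Forty per cent of 44 is about 18 men, leaving 26 women. Sex then explains (18/44) × (26/44) × 0.3² = 0.022, about 2% of variance. Noncentrality becomes 2.843 / √0.98 = 2.872 and power (41 df) 80.1%, a gain of about 1 point. If sex explained 10%, power would be about 83%; if it explained nothing, there would be no gain.

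**4. How prognostic is baseline risk?** This is not stated either, but Table 4 and the improvement thresholds bound it. I simulated the ten items from Table 4's means, SDs and correlations. I assumed normal values, no drift, equal SDs over time and inter-item correlations of 0 to 0.5. Waist was read as inches, because the tabulated values are implausible as centimetres, and one waist cut-off was used for both sexes. The mean baseline z-score explained 7–9% of the score's variance, and the count of abnormal factors 4–8%. A second run under similar assumptions reached 15%. A range of 5–15% is therefore reasonable.

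**5. Adding a baseline summary.** With variance share R², noncentrality is 2.843 / √(1 − R²) on 41 df:

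| R² | Noncentrality | Power |
|---|---|---|
| 0 (t-test, 42 df) | 2.843 | 79.3% |
| 5% | 2.917 | 81.3% |
| 10% | 2.997 | 83.3% |
| 15% | 3.084 | 85.3% |

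**6. Behaviour of the imbalance rule.** The article gives no criterion, so p < 0.05 on each of eight independent candidates is assumed, one of them prognostic. Other inputs: 44 participants, 18/26 by sex, equal allocation within sex, sex effect 0.3 SD, 12,000 trials per cell. Monte Carlo error is about 0.2 points under the null and 0.4 for power.

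| R² of the one prognostic covariate | Type I error: t-test / imbalance rule / fixed model | Power at 1.2: t-test / imbalance rule / fixed model |
|---|---|---|
| 5% | 5.1 / 4.9 / 5.3% | 79.7 / 77.7 / 81.0% |
| 10% | 4.8 / 4.4 / 5.0% | 79.5 / 77.7 / 83.0% |
| 15% | 4.7 / 4.4 / 5.1% | 79.9 / 78.2 / 85.6% |

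The fixed model contains sex and the prognostic covariate. The imbalance rule changed the model in about a third of trials, as expected from 1 − 0.95⁸ = 34%. With 10 or 20 independent characteristics this becomes 1 − 0.95¹⁰ = 40% or 1 − 0.95²⁰ = 64%.

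With stronger covariates (sex 5–20%, ten others jointly 30–60%) the rule's type I error fell to 2.7–4.0%. Over all settings run it stayed below 5%, mostly about 3.5–4.6%. If an analyst reported whichever of the t-test and the triggered model gave the smaller p-value, rejection under the null was 5.2–5.7% in the settings tabulated above.

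**The case against.** The case for leaving the plan alone is respectable. Randomisation makes the t-test valid without covariates. This is a pilot and feasibility trial. The article ties the t-test to the primary outcome and never says the regression supersedes it. The imbalance criterion and covariate list are details that a full analysis plan may supply. The article also says the composite was chosen to account for varying baseline risk profiles.

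Much of this stands, and it limits the size of the point. It does not remove it. Adjustment triggered by imbalance is a rule the article states, placed directly after the primary test, and a criterion supplied elsewhere would still select covariates on the wrong property. A composite lets participants with different risk profiles be scored on one scale, but the chance of improving on each item still depends on where a participant started.

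Three stronger readings are tempting and not supported:

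- **The rule inflates false positives.** Applied mechanically, it does not. Even choosing the smaller p-value gives only about 5.5%.
- **Adjustment would lift power to about 90% or more.** That needs a baseline covariate explaining 25–40% of variance. Table 4's own SDs and correlations, combined with the thresholds, point to about 4–10%, and 15% at most.
- **Table 4 shows that the primary test was meant to be baseline-adjusted**, since it is headed "Minimum detectable effect sizes (4 mo means adjusted for baseline". The improvement score counts changes from baseline and has no baseline value of its own, so the 0.94 correlation cannot belong to it. At 0.40 the t-test has only about 15% power, but that is a separate planning error and no argument for a particular covariate.

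**Conclusion.** The point holds as a modest, cheaply corrected weakness. The primary comparison ignores the factor used in randomisation, and the only route by which covariates enter is chance imbalance, so the model is not fixed in advance. The trial's validity is not in question.

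The power forgone is about 1 point for sex and about 2–6 points for a baseline risk summary (81–85% against 79%). The imbalance rule itself costs 1–2 points against the plain t-test.

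These figures rest on assumptions: a 0.3 SD sex effect, 5–15% of variance explained by the summary, an imbalance criterion of p < 0.05, and Table 4's SD of 1.4 taken only as a planning value. If neither covariate is prognostic, the fixed model gains nothing beyond having been named in advance.

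**What to change.** Before unblinding, name one primary model: linear regression of the 4-month improvement score on arm, sex and the mean z-score of the ten baseline risk factors, signed so that higher is worse (HDL-C reversed). Fit it whatever baseline imbalance is observed. Report the adjusted mean difference with its 95% confidence interval. Delete the imbalance-triggered adjustment and keep the unadjusted t-test as a sensitivity analysis. Only one summary should be named, since leaving a choice of covariate would bring back the same freedom.

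The article reports that the study ran to June 2021, so the data may already be unblinded. In that case, report the sex-adjusted and unadjusted results side by side and label any imbalance-driven model as post hoc.

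The cost is a sentence or two of analysis text and two degrees of freedom. No new data are needed, because sex and all ten factors are collected at baseline.

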## Protocol Management

### Study safety and data management

An Advisory Committee supervised the study design, implementation, and progress. Safety, confidentiality, and comfort of the participants and staff were safeguarded by asking research assistants to wear laboratory coats, gloves, and any other protective gear needed, using private examination rooms, deidentifying or coding samples and data, using secure data collection and storage protocols, and implementing checkpoints during the interview to assess participant’s wellbeing. Adverse events were monitored and reported to the senior investigator team and IRB offices, even if unrelated to study protocols. Any serious adverse condition was immediately referred to the resident clinical staff and/or participant’s health practitioner.

All data were collected using the real-time web-based electronic data capture tool, ‘Research Electronic Data Capture’ (REDCap), hosted at Harvard TH Chan School of Public Health [103]. REDCap separates identifiable and identifiable data using a secure coding system supervised by the team data analyst; all data are anonymized before analysis. The system runs automatic data quality checks through predefined validation parameters. The senior project personnel manage and distribute the data generated from the study with coinvestigators or external investigators observing federal and local policies on disseminating and sharing research results.

### Intervention fidelity and blinding

The research team implemented several strategies to ensure consistency and integrity of protocol implementation. Research assistants were trained on standard operating procedures, including uniform data collection and processing and questionnaire implementation. Instruments were tested and calibrated before and during the study timeline. Toledo Laboratory is a CLIA-certified laboratory that ran internal and external quality control checks daily; monitored assays, reagents, and equipment weekly or as needed; and ran duplicate analysis for 10% of the samples. Participants and all study personnel were thoroughly informed of the importance of observing treatment fidelity. The nutritionist ensured receipt of the text messages daily. Any departures from the protocols were discussed at the bi-weekly team meetings, and immediate corrections were done and monitored when needed.

Three nutritionists delivered the counseling sessions. The following strategies were used to increase fidelity of session implementation: *1*) using a standardized written curriculum and protocol; *2*) having the same senior nutritionist provide and supervise the training; *3*) holding simulated and actual sessions supervised by the senior nutritionist; and *4*) having noninterviewing nutritionists observe actual sessions led by other nutritionists. To monitor fidelity, the team logged the timing and the questions and answers documented during each session, which were subsequently discussed, maintaining blinding.

To assist with blinding, participants were informed that they would follow a healthy eating pattern without identifying the type of diet of each arm. Senior investigators and research assistants taking the measurements were blinded to the participant’s group allocation. Only the nutritionists were aware of group allocation as they provided the nutritional counseling and sent the text messages. The nutritional counseling sessions were conducted in a separate closed room to ensure confidentiality of treatment allocation, which was a different room from where research assistants conducted the measurement visits to prevent study personnel from interacting. Participants were asked not to talk about their diets to the staff, except the nutritionist. Information about randomization status was kept in a separate password-protected spreadsheet, and only the nutritionist had access to it. Biological samples were coded, and the laboratory personnel were blind to study group allocation. Contamination was avoided by excluding individuals with a household member, close relative, or friend already in the study; instructing participants to avoid sharing information about the study or their diet with others; and scheduling single visits (that is, 1 participant at a time) to prevent participants from speaking to each other at the waiting area.

### Process evaluation

The research team monitored internal study protocols, factors extraneous to the study that may have still influenced it, and participants’ feedback bi-weekly. Based on these, minor changes were implemented. For example, the cognitive ability of some interested individuals at the early stages of recruitment was questioned because of inconsistent answers or forgetfulness. A cognitive assessment tool (Montreal Cognitive Assessment) validated for this population [104] was added at the baseline visit before confirming eligibility and randomization (and administered to pending individuals with uncertain cognitive ability). The tool was brief and did not add time or effort burden to the participants. Participants’ feedback was generally positive throughout the study, and no other major changes were made to the protocols, except for COVID-19-related changes.

### The impact of the COVID-19 pandemic

Given the susceptibility of PR to natural and manmade events, like hurricanes, tropical storms, earthquakes, droughts, and sociopolitical disruptions, contingency plans were in place to pause or modify study protocols. On March 16th, 2020, the COVID-19 pandemic was officially declared in PR, interrupting all in-person interventions and research activities as the local government imposed a complete lockdown and other preventive measures. The research team immediately provided participants with culturally relevant, trustworthy information and resources on COVID-19. A weekly COVID-19 questionnaire was implemented to monitor signs and symptoms, testing, management, food access, and behavioral and psychosocial changes during the pandemic for the remaining participants between May and July 2020.

During the pandemic, all ongoing text-based messages continued to be delivered as programmed. However, all scheduled and pending follow-up visits for March–May 2020 were canceled. The time sensitivity of the protocol meant that several enrolled participants were lost during this period. Completion of the questionnaire resumed via phone or video call in May 2020. In June 2020, some restrictions were lifted, and some in-person activities were resumed. Clinic visits were limited to biological samples and clinical measurements following strict safety procedures; participants had the option of having a licensed nurse and research assistant take the measurements at home instead of attending the clinic. Interviews and nutritional counseling sessions were completed by phone or video chat.

Furthermore, a safe and effective protocol was implemented to receive stool samples and other intervention materials from the participant’s car. During this time, the number of times to contact a participant was increased to 10. All new recruitment was suspended and resumed in July 2020 by distributing flyers at safe community sites (that is, supermarkets, pharmacies, and parking lots) and posting on social media. The target sample size had to be adjusted from 100 to 50 participants given the COVID-19 disruptions impact on budget and timeline.

## Discussion

PROMED aimed to determine the efficacy of a Mediterranean-like diet that has been culturally tailored to Puerto Ricans using traditional foods and strategies for decreasing cardiometabolic risk factors. The result from this pilot trial may support observational evidence from cohorts of Puerto Rican adults showing that a MedDiet-like score reflective of typical Puerto Rican dietary preferences is associated with a better cardiometabolic profile. Specifically, a cross-sectional study among adults living in PR showed an adjusted odds ratio (95% CI) of 0.78 (0.63, 0.97) of having abdominal obesity per unit increment of the MedDiet score [22]. Furthermore, in a longitudinal cohort of Puerto Rican adults residing in the mainland US, a higher MedDiet-like score was associated with clinically meaningful and statistically significant 2-y decreases in waist circumference (−0.52 ± 0.26 cm); BMI (−0.23 ± 0.08 kg/m^2^); log-insulin (−0.06 ± 0.02 μIU/mL); log-HOMA-IR (−0.05 ± 0.02), and log-CRP (−0.13 ± 0.03 mg/L) [21].

The MedDiet has been previously adapted and implemented among US-residing Latino adults, but not for Puerto Ricans, who are often grouped in the literature as of Latino ethnic heritage. For example, EnForma was a 3-mo program with no control arm that promoted a MedDiet-style dietary pattern focused on consuming typical Latino foods with high-quality dietary fats (both plant-based and fish) and high-quality carbohydrates [105] Nutritional counseling was given during two face-to-face sessions and two telephone sessions. No specific foods were provided or emphasized. The intervention also recommended increasing physical activity. The main outcome was acceptability, with lifestyle behavior changes at a 3-mo follow-up also reported. Of the 36 participants, 33 completed the program; most were of Mexican heritage, and the majority deemed the intervention helpful and acceptable. Modest improvements were noticed for mean dietary fat quality score [0.5 (95% CI: 0.0, 1.1)] and mean fruit-vegetable servings/d [0.7 (95% CI: 0.1, 1.3)]. EnForma was adapted from the Heart Healthy Lenoir Project, a 2-y randomized controlled trial focused on a Mediterranean-style dietary pattern and increased walking for predominantly African American adults [106]; adaptations included language, use of bilingual/bicultural staff, and culturally-relevant illustrations. EnForma was later translated into EnForma-Diabetes, a 2-mo intervention with similar protocols and outcomes targeting older Latinos with T2D [107]. The program enrolled 21 participants of predominantly Mexican descent and showed high engagement and acceptability and a significant increase in MedDiet score (2.3; 95% CI: 1.0, 3.5).

These studies suggest that MedDiet might be feasible and acceptable to the Latino population. However, the literature is limited to these few examples; these programs were short-term and had a narrow scope. First, the studies did not include a comparison group. Latinos generally respond well to nutrition education programs [108, 109] so it remains unknown if a MedDiet-focused program would be better than general healthy eating messages. Also, the programs were educational only, and nutrition education programs are more effective when coupled with behavioral skills, are based on prior research, or include individual, social and environmental changes; information alone is rarely sufficient to produce behavioral and health changes [110]. PREDIMED provided higher intensity of educational efforts to the intervention group than the control group, yet found that the observed changes in primary outcomes remained the same after accounting for this increased effort [111]. Another shortcoming of the existing programs is that they primarily focus on surface-level cultural adaptations (such as language and use of bilingual staff) rather than structural and deep-structure tailoring that account for the multilayered cultural attitudes and beliefs of the population and which are needed for more effective cultural sensitivity and appropriateness [89, 90, 112]. This is particularly important for Latinos, a diverse group of several ethnic heritages including Puerto Ricans, each with unique food preferences and health-related attitudes [[113], [114], [115]].

PROMED closes several of the existing gaps in the literature. The study included a control group consisting of the healthy eating advice currently used in PR, applied deep-structure cultural components, and provided familiar, accessible, and inexpensive preferred foods. Efficacy studies that typically provide the test food can mitigate structural barriers and add intensity to the intervention [116]. Furthermore, biological outcomes were measured to test the efficacy of the intervention not only on changes in dietary behaviors but also on cardiometabolic outcomes of importance to the PR population, which amplifies the potential for dissemination and implementation. A systematic review of cultural adaptations of the Diabetes Prevention Program found that most of them assessed adoption or feasibility only [117]. The adaptations made to PROMED from the evidence-based PREDIMED are thus expected to be culturally appropriate, acceptable, accessible, and feasible to follow for adults in PR.

PROMED had multiple strengths. First, the study was done in a free-living population, allowing participants freedom of food choices, mealtimes, and frequency of consumption. This approach likens PROMED to a pragmatic clinical trial [118]. Participants were not prescribed a rigid diet and were told they could incorporate the recommendations at their own pace to allow for flexibility within a more real-world setting. The intervention included individual in-person counseling reinforced through subsequent text messages rather than continued educational sessions, deemed less likely to be effective for this population and encompass barriers in time, childcare, and transportation [88, 119]. Text-based interventions were easy to deliver and have proven feasible, acceptable, and efficacious in other interventions for similar Latino groups [92, 120, 121]. Sending texts proved valuable during the COVID-19 pandemic, as the team could continue the intervention without interruptions. Another strength was including deep-structure cultural components that addressed PR-residing adults’ preferences and attitudes toward foods and eating behaviors. Furthermore, PROMED eased structural barriers of access, cost, and familiarity, increasing the likelihood of sustainability of the intervention.

Some limitations were identified in the methodology of PROMED. First, although several measures were taken to safeguard the blinding of outcome assessment, it cannot be guaranteed, given the nature of the study. Only the nutritionists providing the nutritional counseling were aware of group allocation; they did not perform any other study protocol or communicate with other personnel about the participants’ status. However, participants might inadvertently talk about their diet with the staff. Participants familiar with the PR nutritional guidelines or the MedDiet could have deduced their treatment allocation; however, the study information did not specify that it was contrasting these two diets but rather that participants would follow a healthy eating pattern. Another limitation was the COVID-19 delays and changes in protocols. The study lost several participants midstudy, and recruitment of new participants had to be limited, decreasing the final sample size considerably. The timing of the intervention was short, and although changes in blood pressure and lipid markers may be feasible with a healthy diet within 4 mo, weight changes are less salient [106, 122, 123]. The short timing and sample size also prevented from calculating the risk of developing endpoint disease (that is, T2D, hypertension, heart disease outcomes). Longer and larger interventions will be planned to determine if PROMED can be sustained and produce long-term benefits. Additionally, future research should engage community-based participatory research and implementation sciences approaches to strengthen outreach and dissemination of PROMED.

Adherence to a dietary intervention is an important—yet challenging—determinant of its effectiveness [124]. The team applied strategies to increase adherence to the dietary advice and to the food given to the intervention group, such as daily text reminders, takeaway visual aids, underscoring recommended intake amounts, and suggesting recipes or meals to incorporate the food provided. The cognitive function screener also helped exclude individuals with a low likelihood of compliance. The dietary intake questionnaires will allow gauging adherence at the study conclusion. Still, real-time adherence assessments were not included (such as observing participants’ food consumption, collecting daily dietary records, or weighing leftover food), given the short study timeline and its focus on free-living individuals in a real-world setting. Thus, adherence to PROMED would reflect how well individuals comply with dietary advice and recommended foods. Still, to better assess adherence, future studies should consider adding more frequent contact with the nutritionist, collecting periodic detailed dietary records, using supportive aids (such as measuring tools), and collecting objective biomarkers of intake [116, 124]. Further, multidimensional constructs of adherence, that is, behavioral and dietary adherence, may be considered for more accuracy [125]. The stored biospecimens may allow to measure metabolic signatures of MedDiet as objective biomarkers of adherence in the future [126].

The results of this pilot study will support planning and implementing more extensive intervention trials that address the current limitations and help boost the evidence on the healthfulness of a culturally-appropriate MedDiet. If PROMED is proven efficacious in improving cardiometabolic risk factors, dietary intake, and behaviors, the findings may be applied to broader disease-prevention programs and policies in PR. For example, by incorporating PROMED modules into the current healthy eating materials and clinical programs provided by nutritionists in PR; providing or subsiding healthy foods as a replacement for unhealthy ones in government or community food programs; creating incentives for local crops (that is, beans) or other products of superior nutritional value; expanding health insurance coverage of PROMED (or similar nutrition programs) in clinical settings; and [5] developing population-wide health promotion strategies to increase knowledge on how to follow an optimized MedDiet-like tailored to Puerto Ricans.

